### Control group and contamination

The delivery of all intervention components will be under the control of the research team and will not be provided to control group schools during the intervention period. Schools in the control group will receive ‘usual’ (reactive) support which is provided to schools as part of existing service delivery within the respective LHD. This involves the provision of information and resources specific to the PACE program on the existing online portal and includes factsheets, example policies, and templates not related to sustainability. According to evidence and theory [45], such strategies do not address the primary obstacles to sustainability, thus any impact on the primary trial outcome is likely to be minimal. Nonetheless, data regarding schools’ exposure to potential sources of contamination (or co-intervention) will be assessed via items included in teacher and principal follow-up surveys – if evident, potential effects on outcomes will be explored via sensitivity analyses.

### Data collection and management

Principal and teacher data will be obtained through self-report surveys. These will be administered as a pen-and-paper version or using the Hunter New England Population Health (HNEPH) instance of the online data capture tool Research Electronic Data Capture (REDCap) [46, 47], depending on their preference. Management of trial data will be in accordance with a data management protocol, which has been developed and approved by the Advisory Group. Data will be stored securely as per the requirements of the HNE Human Research Ethics Committee and The University of Newcastle Human Research Ethics Committee. Data will only be accessible to primary researchers and statisticians. Confidential participant data will be stored securely and not linked to survey responses.

### Measures

All outcome measures will be collected at baseline, 12- and 24-months post-recruitment.

### Primary trial outcome

#### Sustainment of mean minutes of daily energisers scheduled by classroom teachers over 12- and 24-months

Given the scheduling of energisers consistently possessed the greatest impact on teachers overall scheduling of weekly physical activity in our previous implementation trials [13, 16], and thus increased the likelihood of achieving adherence of the NSW policy [6]; the primary trial outcome will be the between-group difference in the change in mean minutes of energisers scheduled across the school day at 24 month follow-up compared to baseline [18]. Outcome data will also be collected at 12 months in order to describe attenuation patterns. Scheduled daily energisers for each class will be assessed via classroom teacher completion of a daily activity log-book for one full school week (5-days). At the end of each school day during the week of data collection, each teacher will complete a log of the time and occasions they planned physical activity for: energisers, PE, Sport or other structured activities e.g., integrated lessons. The use of teacher logbooks is frequently used in classroom-based obesity prevention interventions, with high response rates (i.e. > 80%) [48, 49] and established reliability [50]. This outcome measure and data collection method has been used in our previous studies assessing teachers’ scheduling of classroom physical activity, with completion rates of ~ 88% [13, 16, 51], which is the premise for use in the current study.

### Secondary trial outcomes

#### Sustainment of mean minutes of weekly physical activity (PE, sport and other structured activities) scheduled by classroom teachers over 12- and 24-months

The difference in the change in mean minutes of overall physical activity and the individual components that make up overall physical activity, including sport and PE, and other planned activities (e.g., active lessons and energisers) implemented by classroom teachers across the school week, assessed via logbooks completed by teachers at 12 and 24-month follow-up compared to baseline.

#### Difference in the change in proportion of school adherence to the 150 min physical activity policy from baseline to 12- and 24-month follow-up

The difference between groups in the change in proportion of schools, from baseline to 12- and 24-month follow-up adhering to the government policy of 150 min of scheduled classroom activity per week.

#### Sustainability determinants to teachers’ scheduling of daily energisers

To assist in understanding the determinants experienced and addressed in this trial we will assess the theoretical factors hypothesised to impact the sustainability of teacher implementation of energisers [21]. Specifically, principals and classroom teachers will complete newly developed measures theoretically informed by the Integrated Sustainability Framework [21] to assess the determinants of sustaining school-based public health interventions at baseline, 12- and 24-months. Each measure was designed to assess the factors perceived by respective stakeholders (executive-level e.g., principal or executive staff member and implementer-level e.g., classroom teacher) as influential to the sustainability of EBIs delivered in the school setting. Using a five-point scale (1 = not at all influential; 2 = slightly influential; 3 = moderately influential; 4 = extremely influential; and 5 = not applicable to me), principals and teachers will be asked to indicate how much the listed factors influence the delivery of daily energisers at their school. The 28-item executive scale to be completed by principals covers four framework domains and focuses on higher organisational and structural-level factors e.g., socio-political context, external funding, external partnerships. Whereas the 42-item implementer scale to be completed by classroom teachers covers all five framework domains and examines factors more relevant to frontline intervention delivery e.g., motivation, capability, training, executive support, and available resources.

### Implementation outcomes

To characterise sustainment, the measures recommended by Proctor et al. [52] of implementation outcomes will also be assessed. This includes;*Acceptability –* The perceived acceptability of each sustainability support strategy will be assessed via a paper or online-based survey completed by principals and classroom teachers of intervention schools at 12 and 24-month follow-up using items from the validated Acceptability of Intervention Measure developed by Weiner et al. [53].*Adoption –* Based upon a previously developed tool from the research team [13, 54], at 12- and 24-month follow-up all intervention and control principals will be asked to report, via paper or online based survey, their school’s adoption for scheduling energisers each day (i.e., proportion of classes at each school scheduling energisers each day).*Appropriateness –* The perceived appropriateness of each sustainability support strategy will be assessed via a paper or online-based survey completed by principals and classroom teachers of intervention schools at 12- and 24-month follow-up using items from the validated Intervention Appropriateness Measure developed by Weiner et al. [53].*Feasibility –* The perceived feasibility of each sustainability support strategy will be assessed via a paper or online-based survey completed by principals and classroom teachers of intervention schools at 12- and 24-month follow-up using items from the validated Feasibility of Intervention Measure developed by Weiner et al. [53].*Fidelity –* Project records as well as post-intervention questionnaires completed by intervention principals, ISC, and teachers will be used to determine the proportion of schools that received and attended to each of the sustainability strategies.*Strategy implementation cost –* Defined as the cost impact of sustainability effort; see economic analysis section below.*Penetration –* This will be calculated, using scheduling data from the teacher survey at 12- and 24-month follow-up, as the number of teachers who schedule daily energisers per school, divided by the total number of teachers expected to schedule daily energisers [52].*Sustainability –* See primary outcome section above.

### Other measures

#### Economic analysis

A prospective economic analysis measuring the incremental cost and outcomes of the sustainability strategies will be undertaken from adapted societal and health service perspectives. Resource use for the intervention and usual practice will be prospectively identified and measured from project records (staff and consumables). Direct costs associated with the intervention are anticipated to include labour (sustainability support), and program materials. Systems to prospectively log and document costs were developed for our previous trials [13, 14, 39, 51] and will be adapted to the proposed study. Incremental cost will be calculated as the difference between intervention and usual care cost. The primary outcome for the economic analysis will align to the trial outcome, which is the between-group difference in the change in mean minutes of energisers scheduled across the school day at 24 months follow-up compared to baseline. A ‘within trial’ economic analysis will assess program value by comparing incremental costs and benefits at the school level across the study arms. Uncertainty intervals will be calculated for the mean incremental cost result and incremental cost effectiveness ratio using non-parametric bootstrapping. Resource use measurement will occur prospectively and continuously over the duration of the trial.

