**Methods:**

A cluster randomised controlled trial will be conducted in 50 primary schools within the Hunter New England, Illawarra Shoalhaven, Murrumbidgee and Northern New South Wales (NSW) Local Health Districts of NSW Australia. Schools will be randomly allocated to receive either usual support or the multi-strategy sustainability intervention that includes: centralised technical assistance from a trained project officer; formal commitment and mandated change obtained from school principals; training in-school champions; reminders for teachers; educational materials provided to teachers; capturing and sharing local knowledge; and engagement of parents, carers and the wider school community. The primary trial outcome will be measured via a teacher logbook to determine the between-group difference in the change in mean minutes of energisers scheduled across the school day at 12 and 24-month follow-up compared to baseline. Analyses will be performed using an intention to treat framework. Linear mixed models will be used to assess intervention effects on the primary outcome at both follow-up periods.

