### Sample size

We are aiming for a sample size of 40 schools (20 per arm). Assuming a comparator mean of 7.08 min of energisers scheduled daily, a standard deviation of 4.88, an average of five classes per school and an intraclass correlation coefficient (ICC) of 0.11, based on our previous trial [13], a sample of 40 schools is sufficient to detect (with 80% power, an alpha of 0.05) a mean difference of approximately 2.38 min of daily energisers.

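### The planned bootstrap interval for the cost-effectiveness ratio will often mix costlier-and-better with costlier-and-worse results, so its limits cannot be read as good to poor value

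*Protocol article*

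**What the plan says.** The protocol article, under Economic analysis, sets the purpose and level of the comparison: "A ‘within trial’ economic analysis will assess program value by comparing incremental costs and benefits at the school level across the study arms". The effect measure is the same as the trial's primary outcome, "the between-group difference in the change in mean minutes of energisers scheduled across the school day at 24 months follow-up compared to baseline". Uncertainty is then to be expressed on two quantities: "Uncertainty intervals will be calculated for the mean incremental cost result and incremental cost effectiveness ratio using non-parametric bootstrapping". The type of bootstrap interval is not stated, nor is the handling of replicates in which the effect is zero or negative.

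The Sample size section gives what is needed to judge how precisely the denominator will be known. It begins "Assuming a comparator mean of 7.08 min of energisers scheduled daily, a standard deviation of 4.88", adds five classes per school and an intraclass correlation of 0.11, and reaches this conclusion about energiser minutes, cut here before its last word: "a sample of 40 schools is sufficient to detect (with 80% power, an alpha of 0.05) a mean difference of approximately 2.38 min of daily".

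**The concern.** The incremental cost-effectiveness ratio is incremental cost divided by incremental minutes. When the bootstrap distribution of the minutes includes zero, the ratio is discontinuous. Replicates just above zero give very large positive ratios, and replicates just below zero give very large negative ones.

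Intervention schools receive project-officer time, meetings and materials, while controls keep existing reactive support, so incremental cost is very likely positive. A negative ratio then means that the programme costs more and achieves less. In numerical order these worst outcomes sit below every favourable positive ratio, so the lower limit is not the optimistic end and the upper limit is not the pessimistic end. A partner organisation that wants to know whether the extra cost buys extra minutes could not read either limit. This arises when the effect is uncertain, which is when a statement of joint uncertainty is most needed.

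**Working it through.** **Inputs.** From the Sample size section: 40 schools (20 per arm), 5 classes per school, SD 4.88 min, ICC 0.11, alpha 0.05, power 80%, detectable difference 2.38 min. The documents give no costs, so these are assumed: mean incremental cost 1000 units per school, between-school SD 300 (800 as a sensitivity case), control cost 0, cost and effect uncorrelated.

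**Step 1: reproduce the protocol's figure.**
- Design effect = 1 + (5 − 1) × 0.11 = 1.44.
- Effective classes per arm = 100 / 1.44 = 69.4.
- SE of the difference = 4.88 × √(2 / 69.4) = 0.828 min.
- With two-sided alpha and 38 degrees of freedom, the detectable difference is 2.38 min, as stated.

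**Step 2: how often the effect interval spans zero.** The normal approximation is Φ(1.96 − δ/0.828) − Φ(−1.96 − δ/0.828). The simulated rates come from resampling schools, with 2,000 trials per effect and at least 1,000 resamples each.

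| True effect (min/day) | Normal approximation | Simulated bootstrap |
|---|---|---|
| 0.4 | 92% | 91% |
| 1.0 | 77% | 73–77% |
| 1.19 | 70% | 65–68% |
| 1.5 | 56% | 51% |
| 2.38 | 18% | 16–18% |

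The abstract gives a different number of schools: "A cluster randomised controlled trial will be conducted in 50 primary schools". With 50, the SE is 0.741 min and the approximate rates are 10% at 2.38 min and 73% at 1 min.

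**Step 3: what the ratio interval then contains.** Suppose the estimated effect is 0.5 min and the incremental cost is 1000.
- The share of replicates with a negative effect is Φ(−0.5 / 0.828) = 27%, all of them costlier and worse.
- With cost held at 1000, the lowest 2.5% of ratios are the replicates with an effect between −0.064 and 0. The highest 2.5% are those between 0 and 0.061.
- The limits are therefore about −1000 / 0.064 and 1000 / 0.061, roughly −15,700 to +16,400 per minute. Simulation with variable cost gives −15,400 to +16,200.
- Both limits are fixed by replicates within about four seconds of no effect. The median ratio is about 890, while the point ratio is 1000 / 0.5 = 2000, because the unfavourable replicates are counted at the bottom of the order.

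**Step 4: coverage of the nominal 95% percentile interval.** Ranges run over the simulations and the two cost SDs.

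| True effect (min/day) | Ratio interval |
|---|---|
| 0.05 | 16–18% |
| 0.1 | 69–73% |
| 0.2 | 87–88% |
| 0.25 | 90–91% |
| 0.4 | 94% |
| 0.5 | 94–95% |
| 0.8 and above | 96–97% |

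Under the same simulated conditions, the bootstrap interval for net benefit covers about 93–95% at every one of these effects.

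**Step 5: would a gate on the effect interval help?** Suppose the ratio interval were reported only when the effect interval excludes zero. Its coverage among reported trials would be 0% at 0.1 min, about 40% at 0.4 min and about 80% at 0.8 min, against 69–73%, 94% and 96% without the gate.

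**The case against.** The strongest reply is that the coverage failure is confined to trivial effects. That stands. A true effect of 0.25 min is 15 seconds a day, about a tenth of the design difference, and the 16–18% figure belongs to an effect of 3 seconds a day. A reader might infer that the planned interval generally fails to cover the true ratio. The figures in Step 4 do not support that.

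Second, the algorithm is partly assumed. The article says only that the bootstrap is non-parametric. This is fair, but percentile-based variants, BCa included, take their limits from the same ordering of raw ratios, so the difficulty does not depend on that choice.

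Third, this is a condensed article, and a health-economics plan may well add a cost-effectiveness plane or an acceptability curve. That also stands. The absence of those displays from the article is not the point and should not be read as a gap. The point is the interval that the article does commit to.

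Fourth, the effect is the trial's primary outcome and will be reported with its own uncertainty, and an interval for incremental cost is already planned. An attentive reader can therefore see whether zero effect is plausible. This lowers the risk of a wrong value-for-money conclusion but does not make the ratio interval readable.

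Finally, the costs are assumed, and the SE is the sample-size section's single-time-point value, not that of the mixed-model change. The exact rates are illustrative.

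**Conclusion.** The point holds as a minor one about interpretation. At the protocol's own precision, the effect interval spans zero in about 18% of trials at 2.38 min, about 65% at 1.19 min and over 90% at 0.4 min or less. In those trials the ratio interval pools opposite conclusions in an order that does not run from good to poor value. Coverage is near nominal from about 0.4 min upward and clearly poor only below about 0.25 min per day.

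The conclusion rests on a positive incremental cost, on an SE of 0.83 min, and on an interval built by ordering raw ratios. It is the same for both assumed cost SDs, and with 50 schools in place of 40. It does not touch the primary outcome or its test.

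**What to change.** In the Economic analysis section, keep the school-level bootstrap of cost-effect pairs and replace the uncertainty interval for the ratio with:

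- bootstrap intervals for incremental cost and for incremental daily minutes, given separately;
- incremental net benefit, λ × incremental minutes − incremental cost, with its bootstrap interval (or an acceptability curve) over a stated range of willingness-to-pay values λ per additional daily minute;
- the bootstrap pairs plotted on the cost-effectiveness plane.

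Report the cost-effectiveness ratio as a point estimate only. Do not make a ratio interval conditional on the effect interval excluding zero, because that selection lowers its coverage at small effects (Step 5).

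The cost is one or two sentences of text. The same replicates serve, and no new data are needed. The downside is that results appear over a range of values instead of as one interval, and the team must choose that range, since the article gives no value per energiser minute.

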#### School characteristics and process data

Data regarding the operational characteristics of schools will be collected using a combination of surveys of the school website as well as survey items completed by school principals and classroom teachers that we have used in previous studies [13, 16]. Project officer records and survey items will be used to record delivery of sustainability support strategies, and exposure of individual schools and teachers to such strategies. Data will be collected, stored, and managed on the HNEPH server using REDCap [46, 47].

### Statistical analysis

All analyses will be undertaken under an intention-to-treat framework. Analyses of outcomes at 12-month follow-up will provide evidence of any immediate impact of the intervention. The 24-month follow-up will provide evidence of sustainment of energiser implementation and will represent the primary end-point. Teachers will be the unit of analysis. Between-group differences in the mean change in the primary outcome will be assessed at each time-point using linear mixed models. Models will include fixed effects for treatment group (intervention vs control), time (baseline, 12-month, and 24-month follow-up), and a time-by-treatment group interaction term. A random level intercept for school will be included to account for the clustered design of the study. A random intercept for teacher nested within school will also be included to account for potential repeated measures by teachers. The linear mixed models will use all available data, assuming missing data is at random.

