### Randomisation and blinding

An independent statistician will use a computerised random number function to randomise schools in a 1:1 ratio to either an intervention or control group. Randomisation will occur following consent and baseline data collection to reduce the risk of selection bias. Block randomisation will ensure group allocation is approximately equal. Allocation will not be stratified by any school-level factor given a lack of clear prognostic factors for the sustainability of physical activity implemented in schools [36, 37]. However, schools will be stratified by time (school phase) and by LHD (jurisdiction) to ensure the allocation across each LHD is approximately equal. Due to the nature and delivery of the intervention, school staff and program delivery staff will become aware of school group allocation. Data analysts will be blinded.

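### The primary model leaves the baseline arm difference free although baseline precedes randomisation, which loses precision, and the 2.38 min power figure belongs to a single-time-point comparison

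*Protocol article*

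**What the plan says.** Under Randomisation and blinding, the protocol article says: "Randomisation will occur following consent and baseline data collection to reduce the risk of selection bias". The primary outcome is the "between-group difference in the change in mean minutes of energisers scheduled across the school day at 24 month follow-up compared to baseline".

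Under Statistical analysis, "Between-group differences in the mean change in the primary outcome will be assessed at each time-point using linear mixed models". The fixed effects are set out as follows: "Models will include fixed effects for treatment group (intervention vs control), time (baseline, 12-month, and 24-month follow-up), and a time-by-treatment group interaction term". Two random effects are named. For schools: "A random level intercept for school will be included to account for the clustered design of the study". For teachers: "A random intercept for teacher nested within school will also be included to account for potential repeated measures by teachers". The 24-month follow-up is the primary end-point.

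The Sample size section plans 40 schools, 20 per arm, with five classes per school, an ICC of 0.11, 80% power and alpha 0.05. It begins "Assuming a comparator mean of 7.08 min of energisers scheduled daily, a standard deviation of 4.88" and arrives at a detectable difference of about 2.38 min. It gives no standard deviation of change and no correlation between baseline and follow-up.

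**The concern.** Because baseline is measured before allocation, the two arms have the same expected baseline mean, and any observed gap is chance. A model with a free group effect at baseline estimates that gap and subtracts it from the follow-up difference, so its sampling error enters the treatment effect. A model with one baseline mean for both arms targets the same quantity with less variance.

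The power calculation is also for a different contrast. It takes a level (7.08) and an SD that is not described as the SD of a change, whereas the primary analysis tests a difference in change. Whether the trial has the stated power under its own model then turns on a correlation that the article does not report. At stake is precision on the primary end-point that could be had without another school or measurement.

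**Working it through.** **Inputs from the Sample size section.** SD 4.88, ICC 0.11, m = 5 classes per school, 20 schools per arm (100 classes per arm), 80% power, alpha 0.05 (taken as two-sided).

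**Reproducing 2.38.** Design effect = 1 + (5 − 1) × 0.11 = 1.44. SE = 4.88 × √(2 × 1.44/100) = 0.828. With 38 df the t quantiles are 2.024 and 0.851, so the detectable difference is (2.024 + 0.851) × 0.828 = 2.381. Power at 2.38 is 79.97%. No baseline term is needed, so this is a single-time-point figure.

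**Variance of the two estimators.** Let R be the correlation of school means between baseline and 24 months. Where the estimate reduces to a comparison of school means, the variance relative to a 24-month-only comparison is:
- planned model (free baseline difference): 2(1 − R);
- common baseline mean: 1 − R².

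The ratio of planned to common-baseline variance is 2/(1 + R), which exceeds 1 for every R below 1: 1.67 at R = 0.2, 1.33 at R = 0.5, 1.11 at R = 0.8. The planned factor equals 1, so that 2.38 is right, only at R = 0.5.

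**What R might be (assumptions).** R = [ICC × c + (1 − ICC) × p × a/m] / [ICC + (1 − ICC)/m], where c is the between-wave school correlation, p the share of teachers measured at both waves and a the teacher autocorrelation. None of c, p and a is in the article. The denominator is 0.11 + 0.89/5 = 0.288.
- c = 0.8, p = 0: R = 0.088/0.288 = 0.306.
- c = 0.8, a = 0.5, p = 1: R = (0.088 + 0.089)/0.288 = 0.615.
- c = 1 (the constant school intercept that the article specifies), p = 0: R = 0.11/0.288 = 0.382.

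With partial overlap the mixed model also recovers within-teacher information, so the factor 2(1 − R) is too pessimistic. At half overlap it would give R = 0.460, a detectable difference of 2.47 and 77% power. The half-overlap row below instead uses the generalised least squares SE for 40 schools, 5 teachers per school at each of three waves, with staying teachers present at all three.

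| Assumption | Planned: detectable difference, power at 2.38 | Common baseline: detectable difference, power at 2.38 |
|---|---|---|
| c = 0.8, no overlap | 2.81, 66% | 2.27, 84% |
| c = 0.8, half overlap | 2.35 (SE 0.819), about 81% | 2.02 (SE 0.703), about 91% |
| c = 0.8, full overlap | 2.09, 89% | 1.88, 94% |
| c = 1, no overlap | 2.65, 71% | 2.20, 86% |

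These rows assume complete data and a covariance model that matches the truth.

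**If the covariance model is wrong.** With school and teacher intercepts only, the model treats the school correlation as 1 and gives baseline too much weight when the true value is low. With no overlap and a true school correlation of 0.3, the common-baseline SE is 0.852 and power 78%; at 0.1, power is about 75%.

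**The case against.** The outcome is defined as a difference in change, and the stated model estimates exactly that. It is a standard and unbiased analysis, and a simple two-mean sample-size calculation is often used for a repeated-measures design. All of this stands, so the point is about efficiency and not validity. The baseline is used, only less well than it could be. Changing the estimator does not move the estimand, because with equal expected baselines the constrained group-by-24-month coefficient is also the difference in change.

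A reader might infer that the trial misses its 80% power. The article does not support that. With half overlap the planned model gives about 81%, and with full overlap 89%. With the constant school intercept that the article specifies and the same teacher autocorrelation, it gives 87% at half and 94% at full overlap. A shortfall appears in these cases only when no teacher is measured twice. The article speaks of potential repeated measures by teachers and lists staff turnover as a common barrier, but gives no overlap figure.

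A reader might also infer that a common-baseline model guarantees 2.38 min at any correlation. It does not: the intercept-only version can fall to 78% or about 75%, as shown, and attrition lowers power further. With 32 of 40 schools retained (20% loss), no overlap and school correlation 0.8, it has about 74%.

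A separate analysis plan could add detail. But the article names the fixed effects explicitly, so the model is stated and not merely left open.

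**Conclusion.** The point holds as a loss of precision and as a mismatch between the power calculation and the analysis. Baseline precedes randomisation, the stated model leaves the arm difference at baseline free, and 2.38 min is a single-time-point figure.

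In every row of the table the common-baseline model is the more precise. At school correlation 0.8 its variance is lower by 35% with no overlap (0.907/1.389 = 0.653) and by 19% with full overlap (0.622/0.771 = 0.807). The gain in power at 2.38 min runs from 5 to 18 percentage points there. Its size rests on the assumed school correlation, teacher autocorrelation and overlap, and on 40 schools. The Abstract gives 50; at that number, with no overlap and school correlation 0.8, power is 76% as planned and 91% with a common baseline.

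A power shortfall is possible but not demonstrated. The change is worth making because it costs almost nothing, not because the planned analysis is wrong.

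**What to change.** Keep the longitudinal mixed model and constrain the baseline mean to be common to both arms: drop the treatment-group main effect and keep time, group by 12 months and group by 24 months. Teachers who join after baseline still contribute. Preferably add a school-by-time random effect, so that baseline is not over-weighted if school levels drift over 24 months.

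In the Sample size section, state that the power figure refers to this 24-month contrast, and show it over an assumed range of school correlation and teacher overlap. Do not state that 2.38 min is met whatever the correlation.

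The cost is one fixed effect removed, one random effect added and a few sentences on power. Recruitment, data collection and the estimand are unchanged. The change should be fixed before unblinded outcome data are examined.

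### The primary model's random intercepts leave clustering of change within schools out of the 24-month standard error, so the test is valid only if schools do not drift differently over time

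*Protocol article*

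**What the plan says.** Randomisation and blinding: an independent statistician will "randomise schools in a 1:1 ratio to either an intervention or control group". The school is therefore the randomised unit.

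Primary trial outcome: the effect is the "between-group difference in the change in mean minutes of energisers scheduled across the school day at 24 month follow-up compared to baseline".

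Statistical analysis: "Teachers will be the unit of analysis". The method for the primary outcome follows: "Between-group differences in the mean change in the primary outcome will be assessed at each time-point using linear mixed models". The fixed effects are group, "time (baseline, 12-month, and 24-month follow-up), and a time-by-treatment group interaction term". The random part has two terms. The first is for school: "A random level intercept for school will be included to account for the clustered design of the study". The second is for repeated measurement: "A random intercept for teacher nested within school will also be included to account for potential repeated measures by teachers". The section names no school-by-time term, school random slope or robust variance.

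Sample size: "We are aiming for a sample size of 40 schools (20 per arm"), with an average of five classes per school, SD 4.88, ICC 0.11, 80% power and alpha 0.05, for a detectable difference of about 2.38 min a day.

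**The concern.** The school intercept is there to handle clustering, and it does so for a comparison of levels at one wave. The primary test, however, is the group-by-time interaction. An intercept that takes the same value at baseline and at 24 months subtracts out of the change. The model then treats two teachers in one school 24 months apart as being as alike, through their school, as two teachers there in the same week.

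The article gives reasons to doubt this. Its Introduction lists leadership support, staff turnover and competing priorities among the main barriers to sustainment. These act on whole schools and in both arms. When they move all teachers of a school together, that shared movement is the error against which a school-randomised intervention has to be judged. If it is left out, the interval for the sole primary contrast is too short and a positive result overstates the evidence.

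**Working it through.** **Step 1. Reproduce the plan's figure.** Inputs from Sample size: 20 schools per arm, 5 classes each, SD 4.88, ICC 0.11, alpha 0.05 (taken as two-sided), power 80%.

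- Design effect = 1 + (5 − 1) × 0.11 = 1.44. Effective number per arm = 100 / 1.44 = 69.4.
- SE of a difference in means = √(2 × 4.88² / 69.4) = 0.828.
- Detectable difference on 38 degrees of freedom (40 schools − 2) = (2.024 + 0.851) × 0.828 = 2.38 min, as stated. The normal approximation gives 2.32.

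This is a calculation for one time point, and it counts school-level variance in full.

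**Step 2. Split the variance.** Total 4.88² = 23.81. School part = 0.11 × 23.81 = 2.62. Within-school part = 21.19.

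Two further quantities are needed, and the article gives neither:
- r, the correlation of a school's level between baseline and 24 months;
- a, the correlation of a teacher's within-school deviation between the two waves (a = 0 behaves like full teacher turnover).

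**Step 3. True variance of the difference in change** (balanced data):

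V = (2/20) × [2(1 − r) × 2.62 + 2(1 − a) × 21.19 / 5]

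The first term is school drift. It vanishes only at r = 1.

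**Step 4. What the stated model estimates.** It treats teachers' changes as independent within a school. The correlation of change between two teachers in one school is

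ρ = (1 − r) × 2.62 / [(1 − r) × 2.62 + (1 − a) × 21.19],

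and the model's variance is too small by the factor F = 1 + 4ρ. F depends on teachers per school and not on the number of schools, so it is the same for the 40 schools in Sample size and the 50 in the Abstract.

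The actual size of a nominal 5% test is about 2 × [1 − Φ(1.96 / √F)].

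**Step 5. Results at a = 0.5.**

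| r | ρ | F | Correct SE (min) | Model SE / correct SE | Type I error |
|---|---|---|---|---|---|
| 1 | 0 | 1 | 0.65 | 1 | 5.0% |
| 0.9 | 0.024 | 1.10 | 0.69 | 0.95 | 6.1% |
| 0.8 | 0.047 | 1.19 | 0.73 | 0.92 | 7.2% |
| 0.5 | 0.110 | 1.44 | 0.83 | 0.83 | 10.2% |

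Worked line for r = 0.5: ρ = 1.31 / (1.31 + 10.60) = 0.110; F = 1.44; 1.96 / 1.2 = 1.633; two-sided tail 10.2%.

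**Step 6. Other values of a.** At a = 0, type I error is 5.6% (r = 0.9), 6.1% (r = 0.8) and 7.8% (r = 0.5). At a = 0.7 it is 8.6% (r = 0.8) and 13.1% (r = 0.5).

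**Step 7. Simulation.** Mixed-model fits of the stated model, with a = 0.5, 5 teachers per school and 60–100% of teachers present at all waves, rejected in 4.6–5.0% of trials at r = 1, 7.3–8.0% at r = 0.8 and 10.5–10.7% at r = 0.5 (2,000 trials per scenario). At r = 0.5 with 60% retention, the empirical SD of the effect was 0.900 against a mean model SE of 0.761. Adding a school-by-time effect and testing on 38 degrees of freedom gave a mean SE of 0.883 and 5.1% rejection in that scenario, and 3.6–5.1% across the scenarios with 5 teachers per school.

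**The case against.** The strongest reply is that the consequence is conditional. A reader might infer that the test simply is anti-conservative and that its type I error exceeds 0.05. The documents do not support that: at r = 1 the size is nominal, and the article reports only an ICC at one time, with no between-wave correlation. With modest drift and high teacher turnover (r = 0.9, a = 0) the size is only about 5.6%. This stands, and the point is worded accordingly.

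Four other tempting readings also fail.

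- **Uneven uptake of the strategies inflates type I error.** It does not. If the intervention does nothing in any school, uneven uptake produces no drift. Under the null only background drift counts, such as the turnover and competing priorities in the Introduction.
- **Precision comes only from within-teacher residual error.** With turnover, teacher intercepts do not fully cancel and add to the model's standard error. It is the school intercept that drops out.
- **The 2.38 min figure exposes a degrees-of-freedom error.** The figure is correct for its one-time-point formula and does not say how the model will be tested. The article states no degrees-of-freedom rule, and an analysis plan commonly supplies one.
- **Larger clusters make it worse.** That is true in principle, but the article plans on an average of five classes per school.

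It could also be said that an unseen analysis plan may add the missing term. However, the article does not leave the random effects open: it names them. A degrees-of-freedom rule added later would not restore a variance component that the model lacks.

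**Conclusion.** The point holds in conditional form. As stated, the primary model does not account for clustering of change within schools, and its standard error is right only if school levels do not drift differently between waves. The article's own account of barriers makes some drift plausible but does not measure it.

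Under the sample-size inputs and a = 0.5, the standard error is about 8% too small at r = 0.8 and 17% too small at r = 0.5. Type I error runs from 5% with no drift to 10–11% at r = 0.5. The problem is milder with a lower teacher correlation and worse with a higher one. Both correlations are assumptions. Only the direction is certain: omitted drift can make the interval too narrow, never too wide.

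**What to change.** In Statistical analysis, keep the school and teacher intercepts and add a random school-by-time effect, or equivalently allow an unstructured school-level covariance across the three waves. Test the 24-month group-by-time contrast with a small-sample degrees-of-freedom method such as Satterthwaite or Kenward–Roger. Fix this before outcome data are analysed.

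The change is one sentence of wording. Intervals become slightly wider, and some power is lost if schools truly do not drift. At r = 1 and a = 0.5, moving from a normal reference to 38 degrees of freedom raises the detectable difference from (1.960 + 0.842) × 0.651 = 1.82 min to (2.024 + 0.851) × 0.651 = 1.87 min. The corrected test can also be a little conservative, as the lowest simulated size of 3.6% shows. The 2.38 min sample-size statement needs no change on this account.
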